## Methods

### Study design

The CHARMED study is a prospective, multicenter, cluster-randomized cross-over study in six EDs in France (NCT02356926). Centers will be randomly assigned to use routine management or systematic cross checking in the first period, and will use the alternative strategy in the second period (Fig. 1). Patients will be recruited in six centers in France. Our institutional review board (Comité de protection des personnes - Paris Ile de France 6) authorized the study without the need of signed informed consent as the study.

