### Definition of key term and endpoints

In accordance to national and international recommendations [1, 2, 15], the following definitions will be used:**Medical Error**: Failure of a planned action to be completed as intended, or the use of a wrong plan to achieve an aim. The severity of an error will be classified using the National Coordinating Council on Medical Error and Reporting (NCCMERP) from A to I [16], as shown in Table 1.**Adverse event (AE)**: An injury that might have resulted from medical care (or lack thereof).**Near Miss**: A medical error that has the potential to cause an adverse event, but did not either by chance or after an intervention. A near miss is an error of severity B, C or D.**Preventable AE**: An AE associated with an error. A preventable AE is a medical error of severity E, F, G, H or I.**Severe Medical Error (SME)**: preventable AE or a near miss.

**Table 1 Tab1:** National Coordinating Council for Medication Errors Reporting and Prevention (NCCMERP) classification of severity of medical errors

A	Circumstances or events that have the capacity to cause error
B	An error occurred but the error did not reach the patient
C	An error occurred that reached the patient but did not cause patient harm
D	An error occurred that reached the patient and required monitoring to confirm that it resulted in no harm and/or required intervention to preclude harm
E	An error occurred that may have contributed to or resulted in temporary harm
F	An error occurred that may have contributed to or resulted in temporary harm and required initial or prolonged hospitalization
G	An error occurred that may have contributed to or resulted in permanent patient harm
H	An error occurred that required intervention necessary to sustain life
I	An error occurred that may have contributed to or resulted in the patient’s death

The primary objective is to assess whether the implementation of Systematic Cross Checking in the ED will reduce the rate of severe medical errors. The primary endpoint is the rate of SME in the seven days following ED visits. Serious guidelines violation (local or national), even in the absence of any documented injury, will be considered as adverse events - As previously described, the subsequent adverse events might not clearly appear in the ED settings, hence its classification as a SME [8]. Hospital or ED re-attendance within the next 7 days will be also considered as an adverse event.

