Secondary endpoints include the followings:Rate of AE and preventable AERate of Near MissSeverity of SMEFactors associated to SME:o Related to patient (age, chief complaint, comorbidities, triage level)o Related to physician (grade, experience, number of physician involved, handoff)o Related to the ED visit (Time of visit, daily occupancy, crowding, waiting time, length of stay, total number of emergency physicians)

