### Statistical analysis

Patient characteristics will be reported in each period, and we will calculate number (rate), mean (standard deviation) or median (interquartile range) when appropriate. Normality will be tested with Kolmogorov-Smirnov method. Proportion of SME will be expressed as percentage and its exact 95 % CI. Characteristics of the two periods will be compared, and differences in any of the following variables will be sought: characteristics of patients and physicians, daily census and severity of patients (triage level, admission rate and ICU admission rate).

The effect of cross-checking will be estimated through a generalized estimating equation (GEE) model, which will take into account the independence of intracluster observations. Factors associated with SME will also be sought with a GEE Model. Severity of SME will be described and compared between the two periods with a chi square test or Fisher exact test when appropriate.

Based on previous literature, we estimate a rate of SME of 10 %, with a potential avoidance rate of more than 50 % [4, 11, 24]. With a hypothesis of a 40 % reduction in the rate of SME (10 % control vs 6 % cross checking), with alpha = 0.05 and beta = 0.2 and accounting for the fact that the cross-over will counterbalance the cluster’s inflation factor, we need to analyze 1584 charts – 140 per period in each center.

All statistical tests will be two-tailed, and a p less than 0.05 will be required to reject the null hypothesis.

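### Severity of SME is tested only among charts with an SME and without allowing for clustering, and the SME proportion gets an exact binomial interval in a six-centre cluster cross-over

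*Protocol article*

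**What the plan says.** The Study design section states: "The CHARMED study is a prospective, multicenter, cluster-randomized cross-over study in six EDs in France (NCT02356926". Each centre contributes one control and one cross-checking period, with 140 charts per centre and period.

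The Statistical analysis section handles the data in three ways:

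- Intervention effect: "The effect of cross-checking will be estimated through a generalized estimating equation (GEE) model, which will take into account the independence of intracluster observations". I read this as intending a model that allows for correlation within centres.
- Group rates: "Proportion of SME will be expressed as percentage and its exact 95 % CI".
- Severity: "Severity of SME will be described and compared between the two periods with a chi square test or Fisher exact test when appropriate".

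Under Definition of key term and endpoints, an SME is a "preventable AE or a near miss". Near misses are NCCMERP categories B to D, and for the upper part: "A preventable AE is a medical error of severity E, F, G, H or I". The secondary endpoints in the same section include, with the list separators lost in the text: "Rate of AE and preventable AERate of Near MissSeverity of SMEFactors associated to SME".

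**The concern.** There are two separate problems. Both lie in methods that the article names, so neither is a detail left to a fuller document.

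**Conditioning on the outcome.** A chart without an SME has no SME severity. The test therefore runs on the SME charts alone, and the trial's hypothesis is that cross-checking reduces those charts by 40%. The SME charts in the two periods are then no longer comparable groups, and the severity mix can move either way:

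- If mild errors are prevented more than serious ones, the remaining SMEs look worse.
- If a cross-check catches an error before it does harm, a preventable adverse event becomes a near miss. It still counts as an SME, and the mix looks better.

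A p-value on the mix does not say whether patients were better or worse off.

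**Clustering.** Chi-square, Fisher and exact binomial methods treat all charts as independent. These charts come from twelve centre-periods, and the same section uses GEE for the intervention effect. At stake are a misleading severity p-value and an overstated precision for the group rates.

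**Working it through.** **Inputs from the article.** SME rates 10% and 6%; two-sided 0.05; 140 charts per centre and period; six centres; categories B-D and E-I. Charts per group: 140 × 6 = 840. (The stated total of 1584 would give 792 per group; both are shown where it matters.) Expected SMEs at 840: 84 and about 50.

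**Assumptions.** The article gives neither the split of SMEs by severity nor an ICC. Both are assumed below.

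**1. Severity mix among SMEs**

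Assume that preventable adverse events fall from 5% to 4.5% and near misses from 5% to 1.5%.

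| | Preventable AE (E-I) | Near miss (B-D) | All SME | Severe share |
|---|---|---|---|---|
| Control | 42 | 42 | 84 (10.0%) | 50% |
| Cross-checking | 38 | 13 | 51 (6.1%) | 75% |

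Uncorrected chi-square = 135 × (42×13 − 42×38)² / (84 × 51 × 80 × 55) = 7.90, p=0.005. Fisher gives p=0.007 and the Yates-corrected chi-square p=0.009. Both absolute rates fall.

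Other assumed splits:

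| Preventable AE | Near miss | Charts per group | Severe share | Chi-square p | Fisher p |
|---|---|---|---|---|---|
| 5% to 4.5% | 5% to 1.5% | 792 | 50% to 75% | 0.005 | 0.006 |
| 4% to 3.8% | 6% to 2.2% | 840 | 40% to 64% | 0.008 | 0.012 |
| 3% to 2.8% | 7% to 3.2% | 840 | 30% to 47% | 0.043 | 0.064 |
| 5% to 3% | 5% to 3% | 840 | 50% to 50% | 1.0 | 1.0 |

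The last row, with equal relative reductions, shows no shift.

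**2. Size of the unadjusted severity test**

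For a cluster cross-over with m SMEs per centre-period, the variance ratio is approximately 1 + (m−1)ρw − mρb, where ρw is the within-period and ρb the between-period ICC. Here m is 14 in control and 8.4 under cross-checking, mean 11.2. I checked it by simulation: 100,000 runs, six centres, 140 charts per centre-period, SME rates 10% and 6%, and a true severe share of 50% in both groups.

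| ρw / ρb | Simulated size (nominal 5%) |
|---|---|
| 0.02/0.02, 0.05/0.05, 0.10/0.10 | 5.0-5.1% |
| 0.01/0.005 | 5.7% |
| 0.02/0.01 | 6.3% |
| 0.05/0.025 | 8.1% |
| 0.10/0.05 | 11.0% |

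The formula at m=14 gives 8.6% and 12.1% for the last two rows. Hence the range of 8-12%.

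**3. Exact interval for a group rate**

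For 84/840 the exact 95% interval is 8.1% to 12.2%. With design effect 1 + 139 × ICC:

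| ICC | Design effect | Width factor (square root) | Interval | Approximate coverage of unadjusted interval |
|---|---|---|---|---|
| 0.01 | 2.39 | 1.55 | 7.1-13.6% | 80% |
| 0.02 | 3.78 | 1.94 | 6.4-14.7% | 69% |

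**The case against.** The strongest reply is that the article already lists the rates of preventable adverse events and near misses as secondary endpoints. Those rates are not restricted to SME charts. In the example, a reader would see both fall beside the primary result and would be unlikely to conclude that cross-checking did harm. This stands as a partial offset. It does not give the planned severity p-value a meaning.

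The reply on clustering is also partly right. Every centre supplies both periods, so stable centre effects largely cancel in the comparison, and the test then keeps its size. The inflation comes only from variation between a centre's two periods, and the article gives no figure for that.

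The exact interval is descriptive. If it is meant only for the rate in these six departments over the sampled days, the design effect does not apply as computed. The intervention effect itself is assigned to GEE.

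A reader might infer that severity will be tested across eight unordered categories, B to I. The article does not say how severity will be grouped, and its own definitions offer a two-level grouping, so that criticism is not supported. A reader might also infer that a beneficial intervention will always appear to worsen severity. It will not: that needs near misses to fall proportionally more than preventable adverse events.

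**Conclusion.** The point holds in limited form. The severity test conditions on an outcome that the intervention is meant to change, and neither it nor the exact interval allows for centres.

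The first part is a matter of design and needs no ICC. Its size depends on the assumed split: from no shift at all to a rise in the severe share from 50% to 75% (p=0.005) while both rates improve.

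The clustering error in the test ranges from negligible, with stable centre effects, to a true size of about 8-12% at ICC 0.05-0.10 with half of it period-specific. The interval is too narrow at any positive ICC if it is to describe more than these centres and days.

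The reach is one secondary endpoint and one descriptive interval. It would be wrong to infer that the primary analysis is compromised, because the primary effect estimate uses GEE and does not depend on either method.

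**What to change.** Three changes to the Statistical analysis section:

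1. Compare severity over all sampled charts, as the proportion with a near miss (B-D) and the proportion with a preventable adverse event (E-I), adding a higher cut such as F-I if counts allow. Use the same centre- and period-adjusted model as for the primary endpoint.
2. Report the severity mix among SME charts descriptively, without a p-value.
3. Give the group SME rates cluster-adjusted confidence intervals, or state that the exact intervals describe only the sampled centres and days.

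A full ordinal model over all categories is not required. With six centres and at least 90% of charts expected to have no SME, it could be unstable.

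The cost is analysis wording and somewhat wider intervals. No new data are needed.

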### Selection of patients

All patients that visit the ED during one of the two periods of recruitment, Monday to Friday between 8:30 am and 4:30 pm, will be screened for inclusion. We chose this time interval as they correspond to period that can be exposed to a cross checking, which will occur at 11:30 am, 2:00 pm and 4:30 pm. Patients with the following will be excluded:Patients whose care is not provided by an EP (for example psychiatrist or maxillo-facial surgeon)Scheduled return attendance to the EDLow severity, defined byTriage level 5 on a 1 to 5 scale (5 being the less severe) [13, 14]Patients referred to a “minor” or “fast track” unitPatients discharged home less than 1 h after first contact with an EP

After the completion of the two study periods, a clinician research technician (CRT) will electronically retrieve the list of patients that attended the ED during the recruiting period. Each center has electronic software that records all admission with the time of arrival and time of discharge. All patients that entered or left the ED within the recruitment period (i.e. Monday to Friday, 9 am to 5 pm, over a specified 2 week period) will be retrieved by their semi-anonymised number, hospital identification number), and the CRT will verify that they have no exclusion criteria. The independent methodology and research department will then randomly select 14 attendances for each of the 10 days of enrollment per period, for a total of 280 visits in each centre.

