### Limitations

There is a potential bias of classification in the adjudication of the primary endpoint. Although the method we will employ to detect and validate AE has already been described, our study may underestimate the incidence of SME. The inherent limitations of chart review is a potential cause of bias, but we are not aware of any other better method.

A Hawthorne effect might occur in the intervention period. Being approached every 3 hours for crosschecking, in the presence of a CRT, may increase the EPs’ awareness of the risk of medical errors and AEs. Crosschecking will not be the only factor that influences EPs in their ED care: being observed and analyzed on their risk of errors, EPs could be more careful, and less prompt to error. To reduce this effect, we will advertise the study in the six participating centers, and a CRT will still be present during the control period to remind emergency physicians that a prospective study on medical errors is taking place. Consequently, we will reduce bias by creating the circumstances that predispose to a Hawthorne effect in both periods of the study.

There is a possibility of contamination bias between the two periods, especially in the centers randomized to have the intervention period before the control period: EPs that found the concept of cross checking useful may pursue its application in daily care. To limit this bias, there will be a 4-week wash out interval between the two periods.

Finally, our study will take place in six urban, academic adults ED. For this reason, we cannot generalize to other settings, especially small rural, or pediatric EDs.

The CHARMED study, a randomized cluster cross-over study, will evaluate the efficacy of the implementation of systematic crosschecking, in reducing the rate of severe medical errors in the ED. CHARMED will be the largest study including unselected ED charts reviewed for detection of adverse events.

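### The sample size treats the cross-over as cancelling the cluster design effect, which needs equal within- and between-period correlations; the stated 80% power is therefore unsupported and probably optimistic

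*Protocol article*

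**What the plan says.** The Statistical analysis section of the protocol article assumes "10 % control vs 6 % cross checking", "with alpha = 0.05 and beta = 0.2", with two-sided testing, and deals with clustering in one clause: "accounting for the fact that the cross-over will counterbalance the cluster’s inflation factor". It concludes that "we need to analyze 1584 charts – 140 per period in each center". It gives no within-period correlation, no between-period correlation and no design effect.

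The design is a "multicenter, cluster-randomized cross-over study in six EDs in France", so there are 12 centre-periods. Under Selection of patients, the coordinating department will "randomly select 14 attendances for each of the 10 days of enrollment per period", which is 140 charts per centre-period. Under Limitations, "there will be a 4-week wash out interval between the two periods". The effect is to be estimated with a GEE model.

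**The concern.** The clause presents as a fact something that holds only under a condition. In a cluster cross-over each centre is its own control, so stable differences between centres drop out of the treatment contrast. Anything that makes charts alike within one centre-period, but is not shared with that centre's other period, does not drop out.

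The article gives reason to doubt that the two periods are interchangeable. Each is a single two-week block, and a 4-week interval separates them. The Statistical analysis section plans to compare the periods on patients, physicians, daily census and severity. The secondary endpoints list occupancy, crowding and the number of emergency physicians as possible factors for severe medical errors. If such factors differ between a centre's two blocks and affect the error rate, IPC falls below ICC and the variance rises.

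At stake is the power claim for the primary endpoint. A non-significant result would be judged against a stated 80%. If the true figure is well below that, the result says less about whether cross-checking works.

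**Working it through.** **Inputs from the article.** Rates 0.10 and 0.06 (difference 0.04, mean 0.08); two-sided alpha 0.05; power 80%; six centres, two periods. The total is 1584 (m = 1584/12 = 132 per centre-period) or 140 × 12 = 1680 (m = 140). ICC and IPC are not given, so every value below is an assumption.

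**1. Reproducing the size without clustering.** The pooled two-proportion formula per arm is

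n = [1.960·√(2·0.08·0.92) + 0.842·√(0.0900 + 0.0564)]² / 0.04² = (0.752 + 0.322)² / 0.0016 ≈ 721,

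or 1442 in total. With continuity correction it is 771 per arm, 1542 in total. The stated 1584 is 2.7% above 1542. It is also close to 1442 plus 10% (1586), but no such allowance is stated. Either way it is about the size of an individually randomised comparison.

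**2. Design effect that the size can absorb at 80% power.**

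- 1584/1442 = 1.10; with continuity correction 1584/1542 = 1.03.
- 1680/1442 = 1.17; with continuity correction 1680/1542 = 1.09.

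Since DE = 1 + (m−1)·ICC − m·IPC ≈ 1 + m·(ICC − IPC), the margin is used up when ICC exceeds IPC by about 0.098/132 = 0.0007 (1584 charts) or 0.165/140 = 0.0012 (1680 charts), without continuity correction.

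**3. Power for the fixed number of charts, normal reference.** With n per arm (792 or 840),

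power = Φ{[0.04·√(n/DE) − 1.960·√(2·0.08·0.92)] / √(0.0900 + 0.0564)}.

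Example: n = 840, ICC 0.01, IPC 0.008. DE = 1 + 139·0.01 − 140·0.008 = 1.27; n/DE = 661.4; (0.04·25.72 − 0.752)/0.3826 = 0.723; power 77%.

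| Assumed ICC | IPC/ICC | DE (m = 132) | Power, 1584 | DE (m = 140) | Power, 1680 |
|---|---|---|---|---|---|
| 0.01 | 1 | 0.99 | 84% | 0.99 | 86% |
| 0.01 | 0.9 | 1.12 | 79% | 1.13 | 81% |
| 0.01 | 0.8 | 1.25 | 75% | 1.27 | 77% |
| 0.02 | 0.9 | 1.24 | 75% | 1.26 | 77% |
| 0.02 | 0.8 | 1.51 | 67% | 1.54 | 68% |
| 0.02 | 0.5 | 2.30 | 49% | 2.38 | 50% |

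**4. Six centres as the independent units.** If inference uses a t reference, the non-centrality parameter is 0.04/√[DE·(0.0900 + 0.0564)/n]. At DE = 1 it is 2.94 for n = 792 and 3.03 for n = 840. Power is then 66% (5 df) or 60% (4 df) at 1584 charts, and 68% or 63% at 1680. Full cancellation with ICC 0.02 (DE 0.98) at 1680 charts gives 69% on 5 df. So the range is about 60–69% with no residual clustering at all.

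**The case against.** A reader might infer that the design cannot deliver 80% power, or that the trial has about even odds of detecting its target effect. The article does not support either reading. It gives no ICC. On a normal reference, full cancellation yields 84–86%, and ICC 0.01 with ratio 0.9 yields 79–81%. Power near 50% appears only in the harsher cells, or at ICC 0.02 with ratio 0.8 when a t reference on 5 df is used (68% becomes 50% at 1680 charts).

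The degrees-of-freedom argument is separate from the quoted clause. The article names a GEE, and a small-sample correction for it may properly be left to the analysis plan, which is not shown. It adds weight but is not needed for the point.

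The source of the period-specific correlation also matters. A pure day effect links only the 14 charts of one day and averages over 10 days, so its inflation is about 1 + 13·ρ(day): 1.13 at ρ = 0.01 (81% at 1680 charts) and 1.26 at ρ = 0.02 (77%). Ratios of 0.5 to 0.8 across all 140 charts need influences that last the whole fortnight. The article makes these conceivable but does not quantify them. Nor does it say that one duty team treats all the charts of a day.

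Finally, that no design effect was applied is inferred from the size, and 1680 charts carry a 17% margin over 1442.

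All of this limits the strength of the conclusion. It does not rescue the clause. A condensed article may omit correlation values, but here it asserts that clustering is counterbalanced, and that assertion is not generally true.

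**Conclusion.** The point stands as an unsupported premise behind the stated power. The cross-over offsets the cluster inflation fully only if between-period correlation equals within-period correlation. The article neither says so nor gives grounds for it, and the chart number leaves room for a gap of only about 0.001 between the two.

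The 80% is therefore unsupported and probably optimistic. How far it is off cannot be fixed from the article: over the assumed correlations tabulated, power runs from 84–86% down to 49–50% on a normal reference. Six-centre t inference would put it at about 60–69% even with full cancellation, if the analysis plan adopts such a method.

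The same sentence also contradicts itself: 1584 charts is 132 per centre-period, while 140 per centre-period is 1680, the number that the sampling scheme yields. Randomisation, endpoint and estimator are not affected.

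**What to change.** In the sample-size paragraph:

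- Replace the counterbalancing claim with the design effect 1 + (m−1)·ICC − m·IPC.
- State the assumed ICC and IPC, each with a range and its source.
- Give the resulting power for the fixed number of charts, and the effect detectable at 80% power under those assumptions.
- Say how inference with six clusters is handled, or point to the analysis plan if it is set there.
- Reconcile 1584 with 140 × 12 = 1680, and use one figure throughout, including the Abstract.

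No extra patients are needed and conduct does not change. The cost is a few sentences and a stated power that is likely to be less favourable.

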**Design:**

The CHARMED (Cross-checking to reduce adverse events resulting from medical errors in the emergency department) study is a multicenter cluster randomized study that aim to evaluate the reduction of the rate of severe medical errors with implementation of systematic cross checkings between emergency physician, compared to a control period with usual care. This study will evaluate the effect of this intervention on the rate of severe medical errors (i.e. preventable adverse events or near miss) using a previously described two-level chart abstraction. We made the hypothesis that implementing frequent and systematic cross checking will reduce the rate of severe medical errors from 10 to 6 % - 1584 patients will be included, 140 for each period in each center.

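### The target of 1584 charts is not 140 per period per centre: six centres with two periods each give 1680

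*Protocol article*

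**What the plan says.** Two places give the total together with a breakdown. The abstract (Design) says "1584 patients will be included, 140 for each period in each center". The Statistical analysis section says "we need to analyze 1584 charts – 140 per period in each center".

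The multipliers stand elsewhere in the article. Study design describes a "cluster-randomized cross-over study in six EDs in France" in which each centre starts with one strategy and "will use the alternative strategy in the second period", so there are six centres with two periods each. Selection of patients sets the sampling rule: the methodology department will "randomly select 14 attendances for each of the 10 days of enrollment per period, for a total of 280 visits in each centre".

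The inputs to the sample size are "10 % control vs 6 % cross checking", "with alpha = 0.05 and beta = 0.2", and the statement that the cross-over offsets the inflation due to clustering. The section also states: "All statistical tests will be two-tailed".

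**The concern.** The number of charts to be analysed is one of the basic figures of a trial. Here it is given as a total and as a number per centre and period, and the two do not multiply out. Both figures stand in the same sentence of running text, in two separate places, so this is neither a broken table nor a superseded value.

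What is at stake is a clear target. A later report of 1584 charts could be read as meeting the plan or as falling 96 short of 140 per period per centre. A report of 1680 could be read as meeting the plan or as exceeding it. The power statement is likewise attached to a total that the sampling rule does not produce.

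**Working it through.** **Inputs, all from the article.** Centres: 6 (Study design). Periods per centre: 2, one per strategy (Study design). Charts per period per centre: 140 (abstract; Statistical analysis). Sampling: 14 per day on 10 days per period, 280 per centre (Selection of patients). Stated total: 1584. Rates 10% and 6%, two-sided alpha 0.05, power 80%, no net cluster inflation (Statistical analysis).

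**Step 1. Can 1584 be reached from the stated inputs?** Pooled two-proportion formula, equal groups, mean rate 0.08, difference d = 0.04:

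n = [1.960 × √(2 × 0.08 × 0.92) + 0.842 × √(0.10 × 0.90 + 0.06 × 0.94)]² / 0.04² = (0.7520 + 0.3220)² / 0.0016 ≈ 720.9, so 721 per group and 1442 in total.

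With continuity correction: n′ = (n/4) × [1 + √(1 + 4/(n × d))]² = (721/4) × [1 + √(1 + 4/28.84)]² ≈ 770.2, so 771 per group and 1542 in total.

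1584 exceeds both results. It is 2.7% above the corrected one (42/1584, taken relative to 1584). The article names no formula, so 1584 is a tenable total for the stated power.

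**Step 2. Does the breakdown match the total?**

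| Route | Arithmetic | Charts |
|---|---|---|
| Stated number per period and centre | 6 × 2 × 140 | 1680 |
| Daily sampling rule | 14 × 10 × 2 × 6 | 1680 |
| Stated number per centre | 6 × 280 | 1680 |
| Stated total | – | 1584 |

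Working back from the total: 1584 / 12 = 132 per period and centre, which is 13.2 per day. At 280 per centre, 1584 would need 1584 / 280 = 5.66 centres. Neither matches the design.

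**Step 3. Size of the gap.** 1680 − 1584 = 96 charts, and 96 / 1584 = 6.1%.

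**Step 4. Power at each total**, from Φ{[0.04 × √n − 0.7520] / 0.3826} with n per group, design effect 1:

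- 1584 charts, n = 792: (1.1257 − 0.7520) / 0.3826 ≈ 0.977, power 83.6%.
- 1680 charts, n = 840: (1.1593 − 0.7520) / 0.3826 ≈ 1.065, power 85.6%.

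Solving the continuity-corrected formula for power at the same group sizes gives 81.2% and 83.5%.

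**The case against.** The strongest defence is that 1584 is the calculated minimum and 140 is the practical figure: 132 per period and centre is 13.2 per day, and rounding up to 14 whole charts gives 140. On that reading nothing is wrong except that a step is missing. It is plausible, and the statistics section does speak of what is needed. But the article does not say it. The abstract says that 1584 will be included and gives 140 as its breakdown, and nothing mentions rounding, a reserve or unusable charts. The defence explains how the mismatch may have arisen; the sentence is still wrong as printed.

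A second objection is that little follows in practice, and this stands. Selection of patients fixes the procedure, and that procedure ends at 1680. Nothing provides for stopping the chart review at 1584.

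A reader might go further and infer that 1584 cannot be derived from the stated inputs, or that it hides an allowance (1440 × 1.10 happens to equal 1584). The article does not support either inference. With continuity correction the inputs give a total close to 1584, no 10% allowance is stated, and 1440 is the result of neither formula above. A condensed article may also leave the details of the derivation to the full protocol.

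**Conclusion.** The inconsistency is real: the abstract and the Statistical analysis section both present 140 per period per centre as the breakdown of 1584, while the design and the sampling rule make it 1680. The difference is 96 charts, or 6.1% of 1584.

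It would be tempting to read this as a power shortfall or as an undefined end to the trial. It is neither. Both totals exceed the stated 80% power, with or without continuity correction, and the sampling procedure is unambiguous. The power figures rest on the plan's own rates and on its assumption that the cross-over cancels the cluster inflation; whether that assumption is sound is a separate question. The multiplication itself rests on no assumption. A headline figure of the trial is misstated in two places and should be corrected, but the practical consequence is small.

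**What to change.** Bring the abstract and the Statistical analysis section into line with Selection of patients: 1680 charts sampled and analysed, that is 140 per period in each of six centres, 280 per centre, 840 per group.

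If 1584 is the calculated minimum, keep it as a separate figure, along the lines of 1584 required and 1680 sampled, with a short statement of why the margin of 96 was taken. The sponsor should give the reason that actually applied; there is no need to construct an inflation factor afterwards to arrive at 1680.

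The cost is a change of wording in two places. Design, sampling and analysis stay as they are.
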